#### 2.3.2. Phase 2—Identifying Intervention Functions and BCTs

##### Method and Analysis

Following phase 1, phase 2 will consist of mapping the COM-B components identified in phase 1 to intervention functions. Within the BCW, intervention functions include nine broad categories such as education and environmental restructuring, which are evidence-based principles of how an intervention can change behaviour. The COM-B components have been linked with specific intervention functions that most are likely to result in behaviour change. This detailed mapping will be conducted by the research team and the PPIE lead, giving an output of intervention functions to target within the RLO.

Intervention functions will also be mapped to individual behaviour change techniques (BCTs) [28] which are “an active component of an intervention designed to change behaviour” [24] such as goal-setting or self-monitoring. We will identify the most frequently used BCTs for each intervention function to present to the caregivers and HCPs for discussion in workshop 3.

The output of phase 2 will be a list of potential content and proposed BCTs for the RLO and the infographic to promote discussion in workshop 3.

#### 2.3.3. Phase 3—Determining Behaviour Change Techniques and Content

Phase 3 will be carried out via workshops 3 and 4.

##### Method and Analysis

*Workshop 3.* We will decide on the most appropriate and feasible intervention components including BCTs and content. The potential content and BCTs developed in phase 2 will be presented to the caregivers and HCPS/support workers by the workshop facilitators. The identified intervention functions will be checked against each of the six APEASE criteria [21]: affordability, practicability, effectiveness and cost-effectiveness, acceptability, side effects/safety and equity. The whole group will consider each individual intervention function against each of the six APEASE criteria to help identify the most appropriate intervention functions to use in the RLO.

The facilitators will present all BCTs that could be considered for each intervention function, identified within phase 2. The number of BCTs will be reduced by using each of the APEASE criteria to find the most appropriate and feasible BCTs to use in the RLO. We will reach a consensus on which BCTs to include in the RLO by ranking each of the ideas by preference to use within the RLO.

The output of the workshop will be a consensus of what should be included in the final RLO and how this should be delivered.

*Workshop 4.* The participants will include caregivers, HCPs and technologists from the University of Nottingham’s health e-learning and media team (HELM) and will use the ranked topic ideas and BCTs from workshop 3 to work on how these can be represented pedagogically and visually in the RLO. The workshop will explore with the participants any analogies, anecdotes, images, videos and personal stories that will engage learners and facilitate their understanding of the ideas and guidance. A0 laminated storyboard templates will be provided for participants to express their ideas in text or drawings. Facilitators will direct the participants using a crib sheet outlining the Theoretical Domains Framework (TDF) with COM-B in order to identify the essential components or ‘active ingredients’, i.e., the visual and graphic elements that represent the knowledge, skills and motivational aspects incorporated into the RLO to bring about the desired behaviour change (responsive feeding)—for example, some of the components that the RLO might address are shown in Table 1.

The output of this workshop will be the creation of a storyboard of caregiver responsive feeding behaviours. In addition, this workshop will concentrate on how to translate non-caregiver behaviours into practice.

Following workshop 4, a prototype of the RLO for caregivers will be developed by the HELM team following the ASPIRE process, including populating a detailed specification from the storyboards which will be peer reviewed by members of the advisory committee. The ‘active ingredients’ in the form of various media assets such as videos and interactivities will be produced guided by the storyboard ideas and inserted into the RLO template along with audio and text components. The design of the RLO will be based on the output from the four workshops integrating the required behaviour changes for responsive feeding. The HELM team will also develop guidance for HCPs/support workers in the form of an infographic, integrating images and key messages from the RLO as appropriate, to accompany the RLO for caregivers. A radar diagram will map the segments of the RLO that relate to the specific domains of the theoretical domains framework as a research output of the study.

#### 2.3.4. Phase 4—Formative and Summative Evaluation

The final phase will be a formative and summative evaluation of the RLO and infographic following the ASPIRE [29] methodology.

##### Recruitment for Evaluation

We will conduct a preliminary evaluation of the functionality, acceptability and usability of the RLO. Caregivers, HCPs and support workers (who were not part of the RLO development) will be recruited for either a formative survey or one of two summative surveys. Potential participants will be emailed a link to the RLO, patient information sheet (PIS), informed consent form (ICF) and respective survey. Participants will be given up to two weeks to access and complete the surveys and will be able to work through the RLO as many times as they require during this two-week period.

Survey 1—Up to 20 caregivers, HCPs and support workers will be asked to review the prototype RLO for content and ease of use.

Survey 2—Up to 30 caregivers will be recruited via Small Steps Big Changes (https://www.smallstepsbigchanges.org.uk/) and public contributors.

Survey 3—Up to 30 HCPs and support workers will be recruited via contacts at the Institute of Health Visiting and the Royal College of Midwives and gatekeepers at local NHS trusts who will be asked to send the survey via email to HCPs and support workers.

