Caregivers seeking health information for their children have reported using the internet as their main source of information and reported high levels of confidence [25], and individuals seeking health information will most often use mobile devices [26]. However, a review of websites on infant health promotion including infant feeding found that the quality, accessibility and readability of the information was poor or adequate [27], highlighting the need for the development of interventions for caregivers and HCPs to be evidence-based, appropriate and useable.

The Public, Patient, Involvement and Engagement (PPIE) group who informed the development of this funding application suggested that any intervention around responsive feeding should utilise digital technology. Therefore, this research aims to develop an app to deliver a behaviour change intervention to caregivers. The chosen approach is a Reusable Learning Object (RLO) which consists of an interactive format with audio, text, animations and videos to promote health behaviour change. To this end, this research will co-create a RLO with caregivers to promote responsive feeding.

The aim of this study is to develop a RLO for caregivers of infants under one year to increase awareness, understanding and use of responsive infant feeding behaviours (CRIB). Improving responsive feeding will contribute to the prevention of obesity at an individual and population level. In addition, this study aims to develop infographic guidance for HCPs and support workers to use with caregivers alongside the RLO.

Objectives:To co-design a RLO to increase caregiver awareness, understanding and use of responsive infant feeding behaviours.To create an infographic for HCPs and support workers to improve their knowledge and ability to support caregivers with responsive feeding.To conduct an initial evaluation of the acceptability of the RLO for caregivers and the guidance infographic for HCPs and support workers.To determine the care pathways within the NHS, social care enterprises and the local authority where the RLO will be offered to caregivers with appropriate support.

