3. I am more likely to feed my baby based on their cues or signs than other ways such as instructions on baby food tins.			
Agree	Neutral	Disagree	
4. The CRIB-RLO resource has improved my confidence in knowing **how** to feed my baby.			
Agree	Neutral	Disagree	
5. The CRIB-RLO resource has improved my confidence in knowing **when** to feed my baby.			
Agree	Neutral	Disagree	
6. The CRIB-RLO resource has helped me understand when it might be more difficult to read my babies signs and cues.			
Agree	Neutral	Disagree	
7. The CRIB e-learning resource has increased my motivation to actively look for and respond to my babies cues during feeding.			
Agree	Neutral	Disagree	

**Table A3 healthcare-12-00029-t0A3:** Survey A3: HCPs implementation into NHS/other organisations.

Part 1 You					
1. Please indicate your main area of work?					
					*Please tick the box*
Health visitor					
Parent support worker					
Midwife					
Children’s Nurse					
Nursery Nurse					
Breastfeeding or lactation consultant					
Other, please state					
2. Please indicate your employing organisation?					
Nottinghamshire Healthcare NHS					
Nottingham City Care Social Enterprise					
United Hospitals Lincoln					
Local Authority					
Charity or NGO					
Higher Education					
Other, please state					
3. Were you involved in the development of the CRIB-RLO resource?					
Yes					
No					
4. If you would like a link to the final resource please provide your email address below					
Part 2 Please provide your views on the CRIB-RLO and the Infographic ^1^					
Please indicate how you feel about the CRIB-RLO and Infographic?					
2. Can you describe any additional effort **you** might need to employ to implement the CRIB-RLO/Infographic into practice?					
3. Is the CRIB-RLO/Infographic a good fit with your own values around how you give infant feeding advice? Please describe any areas where there is conflict.					
4. Do you understand the information contained in the CRIB-RLO/Infographic?					
5. Do you think the CRIB-RLO/Infographic work well together as a way of improving caregiver responsive feeding?					
6. What aspects of the process of providing infant feeding advice in your team/organisation might alter as a result of caregivers having access to the CRIB-RLO?					
7. On a scale of 1-5 how effective do you think the CRIB intervention will be in changing the way caregivers feed their infants?					

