1. Not effective at all	2. Slightly effective	3. Moderately effective	4. Very effective	5. Highly effective	
8. Please let us know why you have given this score?					
9. On a scale of 1-5 how prepared are you to deliver the CRIB intervention to caregivers?					
1. Not prepared at all	2. Slightly prepared	3. Moderately prepared	4. Very prepared	5. Highly prepared	
10. Is there any more training you need to help you prepare to deliver the CRIB-RLO?					

^1^ Questions based on a framework developed by: Sekhon, M.; Cartwright, M.; Francis, J.J. Acceptability of healthcare interventions: An overview of reviews and development of a theoretical framework. *BMC Health Serv. Res.*
**2017**, *17*, 88. https://doi.org/10.1186/s12913-017-2031-8 [36].

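### Objective 3 promises an evaluation of the infographic, but it is not in the listed survey material, no survey item asks about it alone, and neither closed item in Survey 3 names it

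*Protocol article*

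**What the plan says.** The third objective in the Introduction is "To conduct an initial evaluation of the acceptability of the RLO for caregivers and the guidance infographic for HCPs and support workers". Section 2.3.4 opens phase 4 in the same terms: "The final phase will be a formative and summative evaluation of the RLO and infographic following the ASPIRE [29] methodology". The Method section introduces Survey 3 as covering both products in practice, and the Analysis section repeats this.

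The operational text is narrower. Recruitment for Evaluation states the aim as "We will conduct a preliminary evaluation of the functionality, acceptability and usability of the RLO", and it lists what participants receive: "Potential participants will be emailed a link to the RLO, patient information sheet (PIS), informed consent form (ICF) and respective survey". The Method section says that participants engage with the RLO, and it describes all three surveys as evaluating the RLO.

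The instrument for HCPs and support workers is Table A3 in Appendix A. Several of its items treat the two products as one, for example "Do you understand the information contained in the CRIB-RLO/Infographic". One of its two closed items is "On a scale of 1-5 how prepared are you to deliver the CRIB intervention to caregivers". The Method section gives that same item with the RLO, not the intervention, as its object.

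**The concern.** The infographic is one of the study's two outputs, and objective 3 pairs it with its own audience, HCPs and support workers. Survey 3 is the only survey that mentions it. If the listed pack is complete, respondents would be asked about something they had not been given. Even if they do receive it, the items do not let an answer be assigned to one product. A bare yes to the question on understanding could refer to the RLO, the infographic or both. The surveys are described as anonymous and no follow-up is described, so such answers could not be separated later. The Dissemination section plans to circulate the infographic through professional networks and to institutions that train midwives and health visitors, so data on the infographic itself would be useful.

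**Working it through.** No sample-size or power calculation applies, because the article states that no hypothesis is tested. The check is a count of items, followed by a comparison of sections.

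**Step 1: reproduce the stated item count.** The Method section gives eight open and two closed questions for Survey 3. In Table A3, Part 2, items 1–6, 8 and 10 are open (6 + 1 + 1 = 8) and items 7 and 9 are closed (2). The total is 8 + 2 = 10, which agrees.

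**Step 2: classify the ten items by what they ask about.**

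| Items | Type | Product named | Count |
|---|---|---|---|
| 1–4 | open | RLO and infographic, merged | 4 |
| 5 | open | both; asks how well they work as a pair | 1 |
| 6, 10 | open | RLO only | 2 |
| 7, 9 | closed | CRIB intervention, not defined | 2 |
| 8 | open | none; asks for the reason behind item 7 | 1 |
| none | – | infographic only | 0 |

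- Items naming the infographic: 4 + 1 = 5 of 10 (50%). All five also name the RLO.
- Of these, item 5 is properly joint, which leaves 4 of 10 (items 1–4) where merging blurs the answer.
- If items 7–9 are read as covering both products, the joint share is at most 5 + 3 = 8 of 10 (80%).
- Closed items naming the infographic: 0 of 2.

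**Step 3: look at the other surveys.** Survey 1 (Table A1) has nine closed items and one open item, and 0 of 10 mention the infographic. Survey 2 (Table A2, Part 2) has seven items, and 0 of 7 mention it. That is expected for Survey 2, which is for caregivers.

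**Step 4: set the sections side by side.**

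| Place | Scope |
|---|---|
| Introduction, objective 3 | RLO and infographic |
| Opening of section 2.3.4 | RLO and infographic |
| Recruitment for Evaluation, aim and pack | RLO |
| Method, exposure and general description of the surveys | RLO |
| Method, purpose of Survey 3 | RLO and infographic |
| Method, sentence giving the Survey 3 item count | RLO |
| Method, wording of the preparedness item | RLO |
| Table A3, wording of the same item | CRIB intervention |

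**Step 5: follow the analysis through.** The Analysis section plans frequency tables for the two closed Survey 3 items. Neither names the infographic, so from up to 30 respondents no table can be labelled as a result for the infographic. Items 1–5 go to content analysis, where the infographic appears separately only if a respondent chooses to separate it.

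**The case against.** The strongest reply is that the two products form a package. The infographic reuses images and key messages from the RLO and is meant to accompany it, so asking about them together suits a survey on implementation. The questions that name the infographic are open, and open text can be coded by product. The objective asks only for an initial evaluation in an exploratory study. The sentence on the emailed material is a general one covering three surveys, two of which do not concern the infographic, and an article condenses the full protocol.

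Much of this stands, and it rules out several stronger readings that a reader might infer:

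- *Respondents will not see the infographic.* The article does not say that it is withheld. It only fails to list it in the two places where material and exposure are described.
- *Nearly all items merge the products.* Five of ten do so explicitly, one of them rightly, and items 6 and 10 are plainly about the RLO.
- *The infographic half of objective 3 cannot be answered at all.* Content analysis of items 1–5 may give some usable comments.
- *The infographic has no formative review.* The content check by public contributors, experts and a health-visiting group would cover messages that it shares with the RLO. What is not described is a review of the infographic as a product in its own right.

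The reply does not meet two points. Appendix A prints the items themselves, so their wording is not a matter of condensation. And the package argument does not explain why the intervention in the closed items is undefined, or why the article's text and Table A3 give different objects for the same item.

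**Conclusion.** The mismatch is real but moderate. The article promises an acceptability evaluation of the infographic, while its stated material and exposure cover the RLO only. The printed surveys contain no item on the infographic alone (0 of 10 in Survey 3, 0 of 10 in Survey 1), and 0 of 2 closed Survey 3 items name it. Its acceptability can therefore be learned only incidentally from open answers and cannot be reported quantitatively.

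The conclusion on the items rests on Table A3 being used as printed. The conclusion on supply is weaker, because it rests on the article's list being complete for Survey 3. If the infographic is in fact sent, that part becomes a one-line clarification and the item problem remains. The point should be put right before Survey 3 opens, but it is not a condition for the study to proceed.

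**What to change.** 1. In Recruitment for Evaluation and in Method, list the infographic among the Survey 3 material and state that respondents view it before answering.
2. Ask closed items 7 and 9 once for the RLO and once for the infographic, and make the preparedness item read the same in the Method section and Table A3.
3. Give items 1–4 separate RLO and infographic prompts. Keep item 5 joint.
4. Optionally, let the HCPs and support workers in Survey 1 review the infographic as well.

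**Cost.** Splitting items 1–4 adds four items and splitting 7 and 9 adds two: 4 + 2 = 6, taking Part 2 from 10 to at most 16. Item 8 can stay as one question that asks for the reason behind both scores. Four of the six additions are open text, so completion time should be tried out against the article's limit of 20 minutes per survey. If it runs over, steps 1 and 2 matter most, since they settle what was seen and allow a frequency table for each product. They add only two items.

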##### Method

In the first step of the formative evaluation, public contributors, content experts and members of the healthy weight/healthy nutrition group at the Institute of Health Visiting will be asked to evaluate the proposed content to ensure that it is accurate. The public contributors include caregivers from a diverse range of backgrounds who have made different feeding choices (breast and/or formula). The RLO specification will be amended following this evaluation, and the content will be uploaded to the media platform. The prototype will be evaluated by public contributors to ensure that it is fit for purpose by looking at the fit between the content and media.

Next, an initial analysis will be conducted after completing the RLO through three online, anonymous surveys evaluating the acceptability and usability of the RLO. Participants will view and engage with the RLO, which typically takes 15–20 min, although they can review sections as many times as they wish. The anticipated time for completion of each survey is no more than 20 min.

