*Survey 1* (formative) responses will explore the usability of the RLO content and functionality and will be completed by caregivers, HCPs and support workers. The questions have been adapted from a survey tool by Johnson et al. exploring the usability of an e-learning resource to improve the knowledge and confidence of teachers working with children born pre-term [35]. Survey 1 (see Appendix A Table A1 survey A1) will consist of 9 closed questions with responses of agree, neutral or disagree to questions such as “the CRIB-RLO resource held my interest”.*Survey 2* (summative) (see Appendix A Table A2 survey A2) will be completed by caregivers and will ascertain the impact of the RLO on caregivers in terms of changing behaviours related to responsive feeding. There will be 7 closed questions on a 3-point scale from agree, neutral and disagree, including questions such as “The CRIB-RLO resource has improved my confidence in knowing how to feed my baby” and “The CRIB-RLO resource has increased my motivation to actively look for and respond to my babies cues during feeding”.*Survey 3* (summative) (see Appendix A Table A3 survey A3) will be completed by HCPs working with caregivers of infants and will explore the implementation of the RLO and infographic in practice within the NHS and other organisations. The questions have been developed based on a the Theoretical Framework of Acceptability (TFA) developed by Sekhon et al. [36]. The TFA can be used to evaluate the prospective and retrospective acceptability of healthcare interventions by both intervention deliverers and intervention participants. Preliminary reliability testing on the Sekhon et al. TFA adapted for examining the implementation of a telephone-assisted coaching framework revealed three main factors. These are affective attitude and effectiveness (Cronbach’s alpha 0.9, coherence and understanding (0.77), perceived burden (0.85), and suggesting an appropriate level of internal consistency for each construct [37].

Survey 3 will include a mixture of eight open and two closed questions on the implementation of the RLO in practice. Open questions include those such as “Can you describe any additional effort you might need to employ to implement the CRIB-RLO/Infographic into practice?” and closed questions such as “how prepared are you to deliver the CRIB RLO to caregivers?” with a 5-point Likert scale ranging from not at all prepared to highly prepared.

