##### Analysis

Survey responses will be downloaded to an Excel/Sav file.

Survey 1 responses evaluating RLO content, functionality and usability will be analysed with descriptive statistics in the form of frequencies and percentages. The data will be categorised to highlight areas of function or content that require amending.Survey 2 responses examining the impact and usefulness of the RLO on caregivers will be analysed with frequency tables and descriptive statistics. Data from the closed questions will be analysed to examine the impact of the RLO on changing behaviours related to responsive feeding.Survey 3 responses from HCPs exploring the implementation of the RLO and infographic will be a mixture of quantitative and qualitative data. The quantitative data from the two Likert scale questions will be analysed with frequency tables and descriptive statistics. The qualitative data gathered from the open questions will be analysed using content analysis [34].

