## Appendix A

**Table A1 healthcare-12-00029-t0A1:** Survey A1: Usability of the CRIB-RLO.

Part 1 The CRIB-RLO resource ^1^ *Please indicate the extent to which you Agree, are Neutral or Disagree, with the following statements*		
The CRIB-RLO resource held my interest.		
Agree	Neutral	Disagree
2. I enjoyed using the CRIB-RLO resource.		
Agree	Neutral	Disagree
3. I found the CRIB-RLO resource easy to use.		
Agree	Neutral	Disagree
4. The visual elements added to my understanding of the topic.		
Agree	Neutral	Disagree
5. The audio commentaries were engaging.		
Agree	Neutral	Disagree
6. The case studies were engaging.		
Agree	Neutral	Disagree
7. I would prefer to use the CRIB-RLO resource than read written information.		
Agree	Neutral	Disagree
8. It was clear from the learning objectives what was in each section.		
Agree	Neutral	Disagree
9. I would recommend the CRIB-RLO resource to other caregivers or healthcare professionals/support workers.		
Agree	Neutral	Disagree
10. If you Disagree with any of the above statements, please add your suggestions for improving this resource?		
Final Version 1.1, 04/07/2023, IRAS 326807, FMHS 238 0323		

^1^ Questions derived from a survey tool used by: Johnson, S.; Bamber, D.; Bountziouka, V.; Clayton, S.; Cragg, L.; Gilmore, C.; Griffiths, R.; Marlow, N.; Simms, V.; Wharrad, H.J. Improving developmental and educational support for children born preterm: Evaluation of an e-learning resource for education professionals. *BMJ Open*
**2019**, *9*, e029720. https://doi.org/10.1136/bmjopen-2019-029720 [35].

**Table A2 healthcare-12-00029-t0A2:** Survey A2: Impact on caregivers.

Part 1 You			
Please indicate if you are a caregiver or a member of the CRIB public contributors group?			
*Please tick the box*			
Caregiver			
Public contributor			
If you are a caregiver, do you have a child less than one year old?			
Yes			
No			
2. Were you involved in the development of the CRIB-RLO resource?			
Yes			
No			
3. If you would like a link to the final resource please provide your email address below			
Part 2 Your learning			
*Please indicate the extent to which you Agree, are Neutral or Disagree, with the following statements*			
The CRIB-RLO resource has improved my understanding of when my baby is hungry and when they are full.			
Agree	Neutral	Disagree	
2. I am more likely to feed my baby based on their cues or signs than other ways for example, other people’s advice.			
Agree	Neutral	Disagree	

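### Survey 1 mixes caregivers and professionals on an anonymous form with no role question, so caregiver reactions on interest, enjoyment, ease of use, preference and recommendation cannot be separated

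*Protocol article*

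**What the plan says.** The third objective in the Introduction of the protocol article is "To conduct an initial evaluation of the acceptability of the RLO for caregivers and the guidance infographic for HCPs and support workers".

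Section 2.3.4 provides for "three online, anonymous surveys evaluating the acceptability and usability of the RLO". They differ in audience:

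- **Survey 1 (formative, Table A1).** Recruitment for Evaluation states: "Up to 20 caregivers, HCPs and support workers will be asked to review the prototype RLO for content and ease of use". No number per group is given. The Method text says the responses "will explore the usability of the RLO content and functionality and will be completed by caregivers, HCPs and support workers", and that the survey "will consist of 9 closed questions with responses of agree, neutral or disagree".
- **Survey 2 (summative, Table A2).** Caregivers, up to 30.
- **Survey 3 (summative, Table A3).** HCPs and support workers, up to 30.

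The Analysis text for Survey 1 reads: "Survey 1 responses evaluating RLO content, functionality and usability will be analysed with descriptive statistics in the form of frequencies and percentages". A further sentence says the data will be sorted to show what needs changing. No split by respondent type is mentioned. Content analysis is named only for the open questions of Survey 3.

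The last closed item of Table A1 is "I would recommend the CRIB-RLO resource to other caregivers or healthcare professionals/support workers", so the form itself expects readers of more than one type. Item 10 is free text: "If you Disagree with any of the above statements, please add your suggestions for improving this resource".

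**The concern.** Respondent type is asked in the two surveys aimed at one audience each, and not in the one survey that mixes audiences. The learning object is meant for caregivers, and the third objective names them. If caregivers and professionals react differently to the prototype, a pooled percentage can hide the difference, and amendments would follow from an unknown mix of users.

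This is not detail that an article would leave to a fuller document. Table A1 is printed item by item and carries a final version label. Nor can an analysis plan repair it later, because anonymous answers cannot be split by a variable that was never collected.

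A smaller matter concerns item 10, the only item that asks what should be improved. The survey description does not mention it, no qualitative method is named for it, and its wording invites only those who disagree.

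**Working it through.** The plan states no figure to reproduce: section 2.1 says that there is no hypothesis test and that no sample size was calculated. The check is a comparison of the three forms, followed by an illustration.

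**Step 1. The forms side by side (Appendix A).**

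| | Survey 1 (A1) | Survey 2 (A2) | Survey 3 (A3) |
|---|---|---|---|
| Audience | caregivers, HCPs, support workers | caregivers | HCPs, support workers |
| Respondent-type question | none | caregiver or public contributor | main area of work |
| Interest, enjoyment, ease of use | items 1–3 | none | none |
| Preference over written information | item 7 | none | none |
| Recommendation | item 9 | none | none |
| Main content | usability | understanding, intention, confidence, motivation | implementation |

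Table A1 has 9 closed items + 1 open item = 10 items, and none of them asks about role.

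**Step 2. What a pooled count says about caregivers.** Let N be the number of respondents, a the pooled number who agree with an item, and c the number of caregivers. If only N and a are known, then for a given c the caregiver agreement rate lies between

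max(0, a − (N − c)) / c and min(a, c) / c.

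N = 20 is the stated maximum. Both a and c are assumptions, since the article gives neither.

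| Pooled agree | Caregivers c | Lowest rate | Highest rate |
|---|---|---|---|
| 16/20 (80%) | 5 | (16 − 15)/5 = 1/5 = 20% | 5/5 = 100% |
| 16/20 (80%) | 7 | (16 − 13)/7 = 3/7 = 43% | 7/7 = 100% |
| 16/20 (80%) | 10 | (16 − 10)/10 = 6/10 = 60% | 10/10 = 100% |
| 16/20 (80%) | 14 | (16 − 6)/14 = 10/14 = 71% | 14/14 = 100% |
| 14/20 (70%) | 10 | (14 − 10)/10 = 4/10 = 40% | 10/10 = 100% |
| 18/20 (90%) | 10 | (18 − 10)/10 = 8/10 = 80% | 10/10 = 100% |

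In a mixed sample the two bounds meet only when everyone agrees (a = N) or nobody does (a = 0). For any other result the caregiver rate is not determined. The form does not record c either, so a reader would not know which row applies.

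**Step 3. Item 10.** The Method text counts nine closed questions, which matches the nine closed items, and leaves out the open one. Frequencies and percentages do not suit raw free text. The sentence on sorting the data could cover it, but names no method.

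**The case against.** The strongest reply is that Survey 1 is a formative check and not an estimate of caregiver acceptability. It asks users about content and ease of use so that the prototype can be amended, and for that purpose a complaint from any user is useful. The article promises no caregiver percentage from Survey 1, and it assigns acceptability and usability to the three surveys together. Caregivers are also heard elsewhere: in the co-design workshops, among the public contributors who check the prototype, and in Survey 2. With at most 20 respondents in three groups, an even split gives about seven per group (20/3 ≈ 6.7), so tables by role would be thin.

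Much of this stands, and it limits the point. Four stronger readings are tempting but not supported:

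- **A reader might infer that acceptability for caregivers cannot be assessed at all.** It can in part. Survey 2 gives caregiver-only data, which the Analysis text describes as covering impact and usefulness. What is lost is narrower: the five aspects in Step 1.
- **A reader might infer that item 10 falls outside the analysis, or that the text and Table A1 disagree on the number of questions.** The sentence on sorting the data can cover item 10, and the count of nine closed questions is literally correct. The open item is only left unmentioned.
- **A reader might suppose that professionals find e-learning easier, so that pooling flatters the result.** The article gives no support for this. The Introduction reports that caregivers rely mainly on the internet for health information and with high confidence. No direction of bias is claimed here.
- **A reader might take the low ends of the ranges as likely.** They are extremes, reached only if every professional agrees. They show that the caregiver rate is undetermined, not that it is poor.

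The reply does not meet the core of the point. Separate links for each group would solve the problem, but none is described, and role cannot be added after anonymous collection.

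**Conclusion.** The point holds for Survey 1. As printed, the plan would leave caregivers' views on interest, enjoyment, ease of use, preference over written information and recommendation inseparable from those of HCPs and support workers, although the third objective names caregivers. The size of the loss depends on the mix of respondents and on the answers: under the assumed counts, the range for caregiver agreement is from 20 percentage points wide (18/20 agreeing, 10 caregivers) to 80 points wide (16/20 agreeing, 5 caregivers).

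Severity is minor to moderate. The survey is formative and descriptive, no test or sample size is affected, and Survey 2 remains a caregiver-only source on impact and usefulness. The conclusion assumes that Table A1 is the complete form and that respondents are not separated by some means the article leaves out.

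**What to change.** 1. Add one tick-box to Table A1 asking whether the respondent is a caregiver, an HCP or a support worker.
2. In the Analysis text, state that Survey 1 frequencies will be shown by role, as counts with denominators and without comparison between groups.
3. Alternatively, repeat Table A1 items 1–3, 7 and 9 in the caregiver-only Survey 2.
4. As a minor addition, mention open item 10 in the description of Survey 1 and state that its answers will be content-analysed as in Survey 3. Consider inviting suggestions from Neutral as well as Disagree respondents.

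The cost is one question, a short extra table and a few words of text. Cells will be small, which is acceptable for descriptive counts. The alternative in step 3 avoids splitting Survey 1 but adds five items to Survey 2. The role question has to be in place before Survey 1 opens.
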